
**Figure 2 nop2119-fig-0002:**
[figure not shown]
Intervention booklet note. a, cover; b and c, introduction; d, oncologist narrative/certainty Section; E and F, survivor narratives/certainty section; G, accessibility section; H, importance section

#### Attention control arm

3.2.5

Participants in the attention control arm will receive a similar booklet focused on diet instead of exercise. The diet booklet includes one oncologist and one survivor narrative, created by the research team.

#### Measures

3.2.6

Demographic data will be collected by medical chart review and participant interview. Outcome data will be collected through researcher notes, online surveys and a waistband accelerometer, Fitbit^®^. The measurement time points, variables and data sources that will be used to address study aims are detailed in Figure 3.

**Figure 3 nop2119-fig-0003:**
[figure not shown]
Variables and data sources to assess study aims at each measurement point

##### Feasibility

Recruitment and retention of participants, use of Fitbit^®^ as an objective exercise measure, and intervention booklet fidelity will be explored to assess feasibility. The number of potential participants approached, reasons for ineligibility, or declining participation and completion of measures at each time point will be documented to assess recruitment and retention. Notes detailing communication with participants and data from Fitbit^®^ accounts will be collected to assess feasibility of using Fitbit^®^ as an objective exercise measure. To evaluate intervention fidelity, the research team constructed nine quantitative and five qualitative questions (Table 1) that were included in 4‐week postintervention measures for the intervention arm.

**Table 1 nop2119-tbl-0001:** Intervention fidelity questions included in 4‐week postintervention questionnaires

Quantitative fidelity questions (Likert scale rating 1 = not much to 5 = a great deal)
1. How much did the pamphlet make you think about how the benefits of exercise may apply to you as a cancer survivor?
2. How much did the pamphlet make you think about why the benefits of exercise are personally important for you?
3. How much did at least one of the survivor's stories resemble your own experience with breast cancer treatment and side effects?
4. How much did both of the survivors’ stories resemble your own experience with breast cancer treatment and side effects?
5. How much did at least one woman's stories make you feel that if you exercise you will experience benefits?
6. How much did the survivor's stories make you believe that you can exercise for at least 150 min per week at a moderate to strenuous intensity?
7. How much did the oncologist's story make you feel that if you exercise you will experience benefits?
8. How much did the oncologist's story make you believe that you can exercise for at least 150 min per week at a moderate to strenuous intensity?
9. How much did the pamphlet increase how often you think about the reasons you want to exercise?
Qualitative questions
1. Please write the parts of the stories that you most related to or that you found most memorable.
2. What did you do, if anything, that helped you think more often and remember your reasons to exercise?
3. What did you find most useful about the booklet?
4. What did you find least useful about the booklet?
5. Please write any additional thoughts or comments you have about this booklet.

##### Outcome Expectations

Outcome Expectations (OEs) will be measured using the multidimensional exercise OE measure for breast cancer survivors. This measure assesses the dimensions of accessibility, certainty and importance of 20 items that are possible outcomes of exercise specific to breast cancer survivors, such as decreased recurrence risk. The research team created and pilot tested this measure among a sample of 73 breast cancer survivors. The measure demonstrated excellent reliability (α 0.96–α 0.97) and stability over a 4‐week time period (*r*
_*s*_ = .638–.742).

##### Exercise

Exercise intentions will be measured with Likert scale responses to three questions: (i) How motivated are you to exercise regularly over the next month? 1 = extremely unmotivated to 7 = extremely motivated; (ii) I intend to do everything I can to exercise regularly over the next month 1 = strongly disagree to 7 = strongly agree; and (iii) How committed are you to exercise regularly over the next month? 1 = extremely uncommitted to 7 = strongly committed. These questions have previously shown excellent reliability (α 0.87) in a sample of colorectal cancer survivors (Hirschey et al., 2015). Self‐reported exercise will be measured using the Godin Leisure‐Time Exercise Questionnaire (GLTEQ) (Godin, 2011). The measure demonstrates 59% specificity and 75% sensitivity among breast cancer survivors (Amireault, Godin, Lacombe, & Sabiston, 2015). Exercise will also be measured objectively with a Fitbit^®^ Flex. Fitbit^®^ has demonstrated good reliability and validity for monitoring overground energy expenditure (Adam Noah, Spierer, Gu, & Bronner, 2013). For step count outputs compared to research observer counts, concordance = 0.97–1.00 and interdevice reliability of the step count at all walking speeds = ICC ≥0.95 (Takacs et al., 2013).

### Analysis

3.3

Baseline demographic variables will be compared between the intervention and control arms using *t*‐tests for continuous variables and Chi‐squared tests for categorical variables. Statistically significant differences will be controlled for in all analyses.

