### Design

3.1

This feasibility study is a randomized two‐arm trial. Eligible participants will provide written, informed consent and be given a Fitbit^®^ to wear for 2 weeks to establish baseline activity level. At baseline, they will also complete online questionnaires assessing OEs, self‐efficacy and exercise. Participants will receive an intervention or control booklet via mail and will have 1 week to complete it. Follow‐up measures will be collected at 4‐, 8‐ and 12‐week postintervention using the Fitbit^®^ and online questionnaires.

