#### Sample size

3.2.2

Power analyses for mixed models were performed using the optimal design to estimate detectable effect sizes. The analyses revealed that the required sample sizes for detecting a small (δ = 0.20), medium (δ = 0.50) and large (δ = 0.80) effect size of change in OE importance, certainty and accessibility, with a power of 0.80, at a significance level of α = 0.05, are 944, 154 and 62 respectively. Due to the exploratory nature of this study, 60 patients will be recruited. This sample size will allow for examination of the strength and direction of intervention effects.

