#### Random assignment

3.2.3

Participants will be randomized with equal probability to the attention control or intervention arm. A blinded research assistant will orient patients to the study and facilitate data collection. To reduce performance bias among participants, the study will be introduced as being about important lifestyle information. Participants will be told that they will receive diet and exercise information and be randomly assigned to a group focused more on exercise or more on diet.

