#### Intervention effects

3.3.2

Two‐level multilevel modelling will be done using Proc Mixed with SAS software version 9.4. In the level‐1 model, outcomes will be modelled as a linear function of time (baseline, 4‐, 8‐ and 12‐weeks postintervention) to create growth trends. In the level‐2 model, the growth trends will be modelled as a linear function of arm (intervention vs. control). Models will be constructed for OEs, exercise intentions, subjective exercise and objective exercise. For OEs, each dimension will be modelled individually to determine if intervention effects differed between OE dimensions and the average of all dimensions will also be modelled. The level of significance will be set at 0.05, two‐tailed. Effect sizes will be calculated by dividing each beta coefficient by the square route or residual error variance for each outcome. This value is interpreted similar to Cohen's d in which a small effect is 0.2, a medium effect is 0.5 and a large effect is 0.8 (Cohen, 1988).

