### Limitations

4.1

Several limitations of Moving On must be considered. First, while a strength of the study is that the intervention requires minimal resources, some people may need a more intensive intervention. To increase exercise for some people, intensive approaches such as those that include social support or coaching may be needed. Additionally, while the theoretical framework focuses on two of the most significant predictors of behaviour, many other significant constructs such as barriers are not included. This may result in smaller effects on exercise and will also prevent analysis to control for potential confounders beyond self‐efficacy. Another important consideration is the correlation between diet and exercise behaviour change. Often when a person improves dietary practices, they also improve physical activity levels (Psouni, Chasandra, & Theodorakis, 2016). As the attention control group will receive dietary information, they may improve their dietary practices. This could in turn also lead to unintended increases in physical activity and decrease detection of intervention effects. Finally, selection bias may impact study results because people who have positive attitudes towards exercise and diet may be more likely to enrol in this healthy lifestyle study. These people may have greater motivation to exercise and be more sensitive to the intervention.

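### Covariates for every analysis are chosen by significance tests of baseline demographics between randomised arms, so the models depend on chance imbalance and are not fixed in advance

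*Protocol article*

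**What the plan says.** Section 3.3 (Analysis) sets a two-step rule. First, "Baseline demographic variables will be compared between the intervention and control arms", with t-tests for continuous variables and chi-squared tests for categorical ones. Then "Statistically significant differences will be controlled for in all analyses". Allocation is random: "Participants will be randomized with equal probability to the attention control or intervention arm" (3.2.3). The planned size is 60, so about 30 per arm (3.2.2). The only significance level given for the analyses is in 3.3.2: "The level of significance will be set at 0.05, two‐tailed".

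Section 3.3.2 plans a two-level growth model with time (baseline, 4, 8 and 12 weeks) at level 1 and arm at level 2. No covariate is named there. At least seven models follow: three OE dimensions, their average, exercise intentions, subjective exercise and objective exercise.

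Self-efficacy is measured before the booklet is sent: "At baseline, they will also complete online questionnaires assessing OEs", self-efficacy and exercise (3.1). The Background makes it one of the framework's two drivers of exercise. The Limitations (4.1) remark that leaving out other constructs will "prevent analysis to control for potential confounders beyond" self-efficacy. Self-efficacy appears in neither 3.3 nor 3.3.2.

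**The concern.** A baseline test between randomised arms asks whether an imbalance is larger than chance would usually produce. The useful question for a covariate is whether it predicts the outcome, and the test does not address that. The rule can therefore adjust for a demographic that has nothing to do with exercise while passing over a strong predictor whose imbalance falls just short of significance.

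Because a flagged variable enters all analyses, one chance result changes every model. No one can write down the models before seeing the data. The study's stated output is the strength and direction of effects, to inform a larger trial, so it matters that the estimates come from a model fixed beforehand and use the baseline information already collected.

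This is not a detail left to a fuller document. The article commits to a covariate rule, and an analysis plan that followed it would inherit the weakness.

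**Working it through.** The plan gives no figure on this point, and its sample-size figures do not bear on it. The inputs are 30 per arm (60 in total, 1:1), two-sided 0.05 (taken to apply to the baseline tests too), and four measurement times. The number of demographics is not given, so a range is assumed.

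**1. How large an imbalance is flagged.** The critical standardised difference is t(0.975, 58 df) × √(2/30) = 2.0017 × 0.2582 = 0.52. A strong predictor imbalanced by 0.4 SD is left out; an irrelevant variable imbalanced by 0.55 SD is put in.

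**2. How often chance alone changes the models.** For k independent variables the chance of at least one flag is 1 − 0.95^k.

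| k (assumed) | chance of at least one flag |
|---|---|
| 5 | 23% |
| 8 | 34% |
| 10 | 40% |
| 12 | 46% |

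**3. Whether the rule biases results or inflates the error rate.** A simulation used 20,000 runs per setting, 30 per arm, one continuous outcome, and one baseline covariate correlated r with it (r assumed).

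| r | null rejection, test-then-adjust | power at 0.5 SD: no adjustment | test-then-adjust | prespecified |
|---|---|---|---|---|
| 0.3 | 4.8% | 48% | 48% | 51% |
| 0.5 | 4.5% | 48% | 48% | 58% |
| 0.7 | 3.7% | 48% | 49% | 75% |

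The average estimate was on target under every strategy. The rule is slightly conservative and gains almost nothing over no adjustment. The power columns apply to a single follow-up value. They do not transfer to the growth model, as step 4 shows.

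**4. What a covariate does in the planned growth model.** With complete data and a random intercept, the arm-by-time estimate is the difference between arms in mean within-person slope. A baseline covariate entered only as a main effect explains differences in level between people and leaves that contrast alone. In one simulated data set of this form, the arm-by-time estimate was −0.0149 with standard error 0.0676, both without and with the covariate main effect. Adding covariate × time, where the covariate did not truly predict the slope, gave a standard error of 0.0685. So a gain in this contrast needs the covariate to enter for the slope and to predict it. If it does not, the loss is small.

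**5. What handling the baseline outcome properly gains.** Code the four times 0, 1, 2, 3 (equal spacing assumed), with total variance 1 and within-person correlation ρ.

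- Separate baseline means by arm: the arm-by-time variance is 2(1 − ρ)/(30 × 5), where 5 is the sum of squared deviations of the times.
- Common baseline mean: the variance falls by the fraction 9(1 − ρ)/(14 + 6ρ).

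Section 3.2.6 reports 4-week stability of the OE measure of 0.638 to 0.742. Taking this as ρ:

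- ρ = 0.638: 9 × 0.362 / (14 + 3.828) = 3.258/17.828 = 18%.
- ρ = 0.742: 9 × 0.258 / (14 + 4.452) = 2.322/18.452 = 13%.

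A direct matrix calculation gives the same two values.

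**The case against.** The strongest reply is that the rule hardly touches the result that matters. The hypotheses concern greater increase in one arm, that is, arm by time. As step 4 shows, wrongly including or omitting a demographic main effect leaves that contrast essentially unchanged. This stands, and it limits the harm. It does not defend the rule, which still leaves the models open and, because 3.3 does not say how a flagged variable enters, allows it to enter the slope.

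Three stronger readings are tempting, and the documents do not support them.

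- A reader might infer that choosing covariates by pre-test inflates the 5% level. Step 3 shows no inflation and no average bias; if anything the test is conservative.
- A reader might infer that the plan promises to control for self-efficacy and then fails to. The sentence in 4.1 implies only that self-efficacy could be controlled for, because it is measured. It commits to nothing, and a condensed article need not list every covariate.
- A reader might infer that adding a prognostic baseline covariate would cut the residual variance by its squared correlation with the outcome. That holds for a single baseline-adjusted follow-up value, not for the arm-by-time contrast in 3.3.2.

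It is also fair to say that baseline outcome already enters as the first time point. Adding it again as a predictor would use the same value twice, so the remedy must be a constraint on the baseline means. Finally, the primary aim is feasibility, assessed descriptively, and it is unaffected.

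**Conclusion.** The concern holds in limited form. Section 3.3 fixes a covariate rule driven by chance imbalance. It does not identify prognostic variables, and it leaves at least seven models undetermined until the data are seen. The probability that chance alone alters them is about 23% to 46% for 5 to 12 independent demographics, a count the article does not give.

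The cost is a data-dependent model, possible adjustment for irrelevant variables and forgone precision. The recoverable precision that can be sized is the 13% to 18% reduction in arm-by-time variance from a common baseline mean. It rests on complete data, a random intercept, equally spaced times, and the reported OE stability standing in for the within-person correlation; for the exercise outcomes no such figure is given. The gain from baseline self-efficacy cannot be sized, because the documents do not say how strongly it predicts change.

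Since effect testing is a secondary aim of a feasibility study, the severity is minor to moderate.

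**What to change.** - Delete the test-then-adjust rule in 3.3 and describe baseline characteristics by arm without p-values.
- Prespecify one short covariate set, the same for every model, that includes baseline self-efficacy. Enter it at level 2 for both intercept and slope.
- Constrain the arms to a common baseline mean in the growth model of 3.3.2. Do not add the baseline outcome as a further predictor.
- State that follow-up self-efficacy is not adjusted for. The booklet may change it: fidelity items 6 and 8 in Table 1 ask whether the narratives made participants believe they could exercise.

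The cost is analysis wording, a few degrees of freedom, and a slight rise in standard error if the covariate does not predict the slope. Baseline self-efficacy and the baseline outcomes are already to be collected.

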#### Feasibility and fidelity

3.3.1

Descriptive statistics will be conducted to assess participant recruitment and retention at each time point. Recruitment will be considered feasible if 60 participants are recruited within 6 months, which is an average of one to two participants per week. This target enrolment rate is comparable to previous recruitment rates of breast cancer survivors, to other physical activity interventions, using similar recruitment strategies. For example, in one study, it took 12 months to recruit 40 participants at clinic follow‐up visits (Fields, Richardson, Hopkinson, & Fenlon, 2016), and in another study, it took 23 months to recruit 210 participants through the mail (Befort et al., 2014). Retention will be considered feasible if attrition is less than 17%, which is comparable to other home‐based exercise interventions for breast cancer survivors in which attrition ranged from 13% to 20% (Lahart, Metsios, Nevill, Kitas, & Carmichael, 2016; Pinto, Papandonatos, & Goldstein, 2013; Pinto, Rabin, Abdow, & Papandonatos, 2008; Rabin, Pinto, Dunsiger, Nash, & Trask, 2009).

Fitbit will be considered a feasible objective exercise measure if the percentage of Fitbit data obtained is equal or greater than the percentage of subjective data obtained from online questionnaires. Notes detailing Fitbit^®^‐related interactions between the research team and participants will be reviewed to identify common themes about Fitbit^®^ set‐up and use. Means and standard deviations will be calculated for the quantitative fidelity questions. Qualitative fidelity data will be examined to identify reasons for low scores (defined a priori as ≤2.0 on the five‐point Likert Scale). Common themes that inform the extent to which participants understood, completed and found the intervention booklet useful will be identified.

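### The recruitment criterion misstates its own rate: 60 participants in 6 months is about 2.3 per week, and only one of the two cited benchmarks is close to that

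*Protocol article*

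**What the plan says.** The Background (section 2) makes feasibility the primary aim, and section 3.2.6 lists recruitment among its components. Section 3.3.1 gives the recruitment criterion and, in the same sentence, a translation of it into a weekly rate: "Recruitment will be considered feasible if 60 participants are recruited within 6 months, which is an average of one to two participants per week". The next sentence justifies the level chosen: "This target enrolment rate is comparable to previous recruitment rates of breast cancer survivors". Two examples follow. In one study "it took 12 months to recruit 40 participants at clinic" follow-up visits; in the other "it took 23 months to recruit 210 participants through the mail". The count of 60 agrees with the planned sample in section 3.2.2. The article gives no other recruitment rate and no graded threshold.

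**The concern.** The sentence contains a count, a window and a rate, and any two of them fix the third. Here the stated rate does not follow from the count and window, and the error is in the lenient direction: the rule asks for faster recruitment than the article tells its reader. The two examples meant to show that the target is realistic give rates that differ almost threefold from each other, and both lie below the target.

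At stake is how a prespecified success criterion for the primary aim is understood and reported. A team that monitors accrual against the weekly figure could believe it is on course while heading for 52 or fewer at 6 months. If the mismatch is noticed only once accrual is known, there is room to argue over which figure was meant.

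**Working it through.** **Inputs, all from section 3.3.1.** Target 60; window 6 months; stated rate 1 to 2 per week; clinic study 40 in 12 months; mail study 210 in 23 months.

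**Step 1: try to reproduce the stated rate.** Rate = count / weeks.
- 6 months as 26 weeks: 60/26 = 2.31 per week.
- 6 calendar months (6 × 365.25/7/12 = 26.09 weeks): 60/26.09 = 2.30 per week.
- 6 months of 4 weeks: 60/24 = 2.50 per week.

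Every convention gives more than 2, so the stated range is not reproduced.

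**Step 2: what the stated rate would deliver.** Count = rate × weeks.
- 1 per week: 1 × 26 = 26.
- 2 per week: 2 × 26 = 52, which is 8 short of 60.
- Time to reach 60: 60/2 = 30 weeks (6.9 months) to 60/1 = 60 weeks (13.8 months).

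**Step 3: the benchmarks.** Monthly rate = count / months; weekly rate = monthly rate / 4.348; the target is 60/6 = 10 per month.

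| | Per month | Per week | Expected in 6 months | Months to reach 60 | Target ÷ benchmark |
|---|---|---|---|---|---|
| Clinic study | 40/12 = 3.33 | 0.77 | 20 | 18.0 | 3.0 |
| Mail study | 210/23 = 9.13 | 2.10 | 54.8 | 6.6 | 1.10 |
| Target | 10.0 | 2.30 | 60 | 6.0 | 1.0 |

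**Step 4: side check on chance.** The article gives no accrual model. If enrolments are assumed to be Poisson, the probability of at least 60 in 6 months is:
- below 0.001 at the clinic rate (mean 20);
- about 0.26 at the mail rate (mean 54.8);
- about 0.15 at exactly 2 per week (mean 52);
- about 0.52 at the target rate itself (mean 60).

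The last figure is a reminder that a fixed count within a fixed window is missed about half the time even when the true rate equals the target.

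**The case against.** The best defence is that the sentence contains only one criterion: "Recruitment will be considered feasible if 60 participants are recruited within 6 months". The weekly rate is an explanatory aside with no verdict attached. Whoever applies the rule counts enrolments at 6 months and gets one answer, and the count matches the planned sample. This stands. A reader might infer that the two halves of the sentence can give opposite verdicts on the same data, but the text does not support that, because only the count within the window decides.

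The defence is also right on three further points.
- The mail study's 2.10 per week against 2.30 is a gap of about 10%, and calling those comparable is reasonable. The studies are offered as examples, and nothing shown here describes their number of sites or catchment.
- A threshold above past rates is not an error in itself; how demanding to be is the team's judgement.
- A reader might take the criterion for a go/no-go rule. The article says only that recruitment would be considered feasible and attaches no decision to stop or proceed. The Discussion (section 4) says the results will help refine materials and procedures before a larger study.

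The defence does not remove the arithmetic error, which no other section corrects. Nor does it rescue the clinic study as support for the target. This is not a matter of an article condensing a longer protocol: the figure is stated, and it is wrong.

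**Conclusion.** Wrong as written, and minor. The implied rate is 10 per month, about 2.3 per week (2.5 with 4-week months), against a stated one to two. Even the top of the stated range falls 8 participants short over 26 weeks. The claim of comparability is supported by the mail study (target about 10% higher) and not by the clinic study (target three times as high).

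A reader might go further and conclude that recruiting at a benchmark pace would necessarily be judged infeasible. That is too strong. Expected accrual at either pace falls short of 60, but under the Poisson assumption the mail pace would still reach 60 about one time in four. Only at the clinic pace is a shortfall practically certain.

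The rate and benchmark results rest on the article's own numbers and hold under every month convention tried. Only the probabilities depend on an added assumption, and the verdict does not need them. The sample size, randomization and effect models are untouched.

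**What to change.** Keep 60 within 6 months as the operative criterion. In section 3.3.1, restate the rate as 10 per month (about 2.3 per week). Replace the claim of comparability with the two benchmark rates, 9.1 per month for the mail study and 3.3 per month for the clinic study, and say that the target slightly exceeds the first and is about three times the second.

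Lengthening the window to suit the weekly figure is not advised as the default. It would loosen a prespecified threshold to fit a faulty aside, and it need not even reconcile the range: over 9 months (39 weeks), one per week still gives only 39. If the team did intend one to two per week, it should reconcile the count and window with that rate and record the change before any recruitment data are seen.

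The cost is one or two sentences of text. No design element or analysis changes. The stated target will simply look more demanding than the present wording suggests.

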**Methods:**

Intervention arm participants will be given a theory‐guided booklet that was co‐created by the research team and three physically active breast cancer survivors who exercise to manage late and long‐term treatment effects. Attention control arm participants will be given a similar booklet focused on diet. Participants will have 1 week to complete reading, writing and reflecting activities in the booklets. Study outcomes will be measured through online surveys; exercise will also be measured objectively with a Fitbit^®^. Four weeks postintervention, participants’ thoughts about the usefulness, strengths and weakness of the intervention booklet will be assessed. OEs and exercise will be measured at baseline, 4‐, 8‐ and 12‐week postintervention.

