#### Intervention

3.2.4

The intervention, Moving On, consists of an exercise OE booklet containing narrative messages, writing and thinking activities intended to increase OE dimensions of importance, certainty and accessibility. The booklet provides a global overview of the many and diverse positive outcomes breast cancer survivors may experience from exercise. The booklet cover (Figure 2a) contains the study name, Moving On. This name captures the stage of cancer survivorship and encourages participants to take action by moving, that is, exercising. The cover image was selected because the research team thought it was uplifting and motivational. The woman in the picture is intended to be relatable to many breast cancer survivors because she is of average to slightly above average weight, and her age and race are ambiguous. The first page of the booklet (Figure 2b) introduces the ACS recommendations on diet and exercise for cancer survivors. The second page (Figure 2c) lists outcomes associated with exercise for breast cancer survivors (e.g. decreased fatigue, improved survival). This section aims to increase awareness of the many benefits of exercise for breast cancer survivors. It explicitly states that because one has had breast cancer and treatment, these outcomes may be especially important. To increase OE importance, there is a section (Figure 2h) instructing the participant to select the three outcomes that she would most like to experience from exercise and then elaborate on all the things that will happen if those outcomes occur. OE certainty is primarily targeted in the intervention through three narrative messages, two from breast cancer survivors who exercise regularly and one from an oncologist (Figures 2d–2f). Each survivor narrative is a few long paragraphs, written in first person and includes a photograph of the author. The survivors’ narratives summarize the women's personal stories of: (i) cancer treatments and side effects they experience; and (ii) outcomes obtained as a result of exercise and how achieving these outcomes helped them manage symptoms (e.g. stress, pain). The oncologist's narrative contains: (i) her personal recommendation for breast cancer survivors to exercise; and (ii) outcomes she believes survivors may obtain, based upon current research. Finally, to increase OE accessibility, the booklet instructs participants to identify at least three strategies that could motivate them to think about outcomes they may experience if they exercise regularly (Figure 2g). Suggestions (e.g. reading booklet daily, making a computer screen saver) are provided.

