Regardless of the outcomes of Moving On, information will be gained about what breast cancer survivors do with printed materials that they receive through mail or during clinic visits. Patients are commonly provided written information; however, the extent to which they read and find the information useful is rarely assessed. Due to the continuously increasing demands of breast cancer survivorship care (I. Chopra & Chopra, 2014), it is necessary to test low‐cost, simple methods of disseminating information to patients.

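### None of the 14 fidelity questions directly asks whether the booklet was read or its writing tasks done, although the plan says the data will inform the extent of completion

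*Protocol article*

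**What the plan says.** The Background section makes feasibility the primary aim, and section 3.2.6 (Measures, Feasibility) lists booklet fidelity as one of its components. For fidelity, "the research team constructed nine quantitative and five qualitative questions", set out in Table 1 and placed in the 4-week "postintervention measures for the intervention arm".

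The Abstract describes what participants are asked to do: "Participants will have 1 week to complete reading, writing and reflecting activities in the booklets". Section 3.2.4 (Intervention) specifies two tasks. For the importance dimension there is a section "instructing the participant to select the three outcomes that she would most like to experience from exercise", on which she then elaborates. For the accessibility dimension she names at least three strategies for keeping the outcomes in mind.

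On what will be learned, section 3.3.1 says: "Common themes that inform the extent to which participants understood, completed and found the intervention booklet useful will be identified". The Discussion says that, whatever the results, "information will be gained about what breast cancer survivors do with printed materials", and remarks of written information given to patients that "the extent to which they read and find the information useful is rarely assessed". The Conclusion again says that insight will be gained into how patients use such material.

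**The concern.** The booklet arrives by post and is worked through at home without supervision, so non-use is an obvious way for the intervention to fail. A feasibility study is the place to find that out. If the fidelity survey records only reactions to the booklet, a participant who never opened it and one who read it and was unmoved can return the same low rating.

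Those two situations call for different changes before a larger trial: one concerns delivery and engagement, the other content. The Discussion says the results will guide refinement of both materials and procedures, so the distinction bears on a stated use of the data. Analysis cannot recover it afterwards if the survey did not ask.

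**Working it through.** The main check sets the instrument beside the stated outputs.

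**1. Item count.** Section 3.2.6 gives nine rated and five open questions, 9 + 5 = 14. Table 1 lists 14, so the stated number is reproduced.

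**2. What each item asks.**
- Rated items 1, 2, 5, 6, 7, 8 and 9 (seven items): how far the pamphlet or a story prompted thoughts, feelings or beliefs, or raised how often the participant thinks about her reasons for exercising.
- Rated items 3 and 4 (two items): how closely the survivors' stories resemble her own experience.
- Open item 1: the parts of the stories she related to or remembers. It presupposes reading and does not ask about it.
- Open item 2: what she did, if anything, to keep her reasons in mind. It touches the strategies task but does not ask whether that section was completed.
- Open items 3, 4 and 5: most useful, least useful, other comments.

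Check: 7 + 2 + 5 = 14.

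**3. Items against stated outputs.**
- Whether, or how much of, the booklet was read: 0 of 14 direct; open item 1 indirect.
- Outcomes task done: 0 of 14 direct; no item addresses it.
- Strategies task done: 0 of 14 direct; open item 2 indirect.
- Finished within the allotted week: 0 of 14.
- Found useful: open items 3 and 4 ask this directly, so that part of the stated output is covered.

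**4. Other sources.** Section 3.2.6 names researcher notes, online surveys and the Fitbit as outcome sources. The notes on communication with participants are assigned to Fitbit feasibility there and in section 3.3.1. Return or inspection of the booklet is not mentioned.

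**5. Low scores.** Section 3.3.1 defines a low score as 2.0 or less and turns to the qualitative answers for reasons. With no direct question on use, non-use becomes visible only if the participant volunteers it.

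**6. What a direct item would yield.** Inputs: 60 participants randomized with equal probability, so about 30 in the intervention arm; at the 17% attrition limit in section 3.3.1, 30 × 0.83 = 24.9, about 25. Completion of 70% is an assumption for illustration. The 95% half-width is 1.96 × √[p(1 − p)/n].
- n = 30: 1.96 × √(0.7 × 0.3 / 30) = 1.96 × 0.0837 = 0.164, about ±16 points.
- n = 25: 1.96 × √(0.7 × 0.3 / 25) = 1.96 × 0.0917 = 0.180, about ±18 points.

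This is coarse, but enough to tell wide use from widespread non-use. It describes the remedy and does not measure the defect.

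**The case against.** The strongest reply is that section 3.3.1 promises themes that inform the extent of completion, not a completion rate, and that the Discussion's remark on how rarely reading is assessed describes usual practice and defines no endpoint. That stands: the plan should not be faulted for lacking an estimate it never offers. But themes drawn from volunteered remarks are weak evidence of extent, and extent is what the sentence names.

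A second reply is that relevant data are collected. This also stands in part. A non-reader could not easily supply remembered story content for open item 1, open item 2 allows the answer that nothing was done, and the remaining open items may draw out admissions of non-use. It would be wrong to say that nothing bearing on completion is gathered. The gap is in direct measurement and is complete only for the outcomes task.

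Third, Figure 3, which lists variables and data sources by time point, is not shown and could name another source. The visible text names none, but that caveat remains.

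A reader might infer three stronger points that the document does not support:
- **The intervention arm's extra questions act as a one-sided exercise prompt before weeks 8 and 12.** Both arms repeatedly answer the exercise outcome-expectation, intention and Godin items and wear a Fitbit. Nothing in the document indicates how much the fidelity questions would add to that shared prompting.
- **Non-use dilutes the estimated effect by a known amount.** The document gives no completion rate, so any such figure would rest on an assumed one. Intervention effects are also the secondary aim, where the effect of handing out the booklet, used or not, is relevant to the intended clinic use.
- **Failure to measure use of the control booklet is a defect.** The fidelity output in section 3.3.1 is confined to the intervention booklet, and no stated aim or criterion concerns use of the diet booklet.

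**Conclusion.** The point holds as a mismatch between a fully printed instrument and an output stated for it, within the primary feasibility aim. It is not a complaint about detail left to a fuller document. The size is 0 of 14 items asking directly about reading or task completion, with indirect evidence mainly from two open items. The practical result is that low fidelity scores cannot be reliably divided between non-use and use without persuasion, and that statements about completion and use of printed material would rest on volunteered comments.

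This assumes that Figure 3 adds no completion measure and that booklets are not returned or inspected. The remaining feasibility criteria (recruitment, retention, Fitbit data) are unaffected. The weakness is modest and inexpensive to correct, but should be corrected before the 4-week survey is used.

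**What to change.** Add two to four closed items to the intervention arm's 4-week survey:
- how much of the booklet was read (none, part, all);
- whether the outcomes task was done (yes/no);
- whether the strategies task was done (yes/no);
- whether the booklet was finished within the week (yes/no).

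Report each proportion descriptively with a 95% interval, and read low fidelity scores alongside these answers. Parallel items on the diet booklet for the control arm are optional.

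If the survey cannot be changed, narrow section 3.3.1 to what Table 1 covers, and qualify the statements in the Discussion and Conclusion about use of printed material.

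The cost is about one extra minute per participant in an existing online survey. Self-report may overstate completion slightly, which should be acknowledged when the proportions are reported.
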